
### Intervention

2.11

#### Basic information of the investigational drug

2.11.1

The investigational drug is SXYX, provided as granules. Each bag contains 10.0 g of granules. The granules are manufactured by the Department of Pharmacy (Hospital Preparation Unit), The First Affiliated Hospital of Henan University of Chinese Medicine. The Department of Pharmacy is qualified to prepare hospital-formulated herbal products under Good Manufacturing Practice-like conditions. Store at room temperature (15 °C–25 °C) in a dry and well-ventilated place, protected from light.

#### Drug packaging and labeling

2.11.2

A label will be attached to the packaging of the investigational drug, displaying the following information: drug number, drug name, specification, dosage and administration, lot number, expiration date, precautions, storage conditions, production unit, and the statement “For clinical trial use only”. The packaging and labeling are designed to maintain blinding and randomization; the label will show only the drug number and will not reveal the patient's treatment allocation (SXYX or placebo).

#### Treatment regimen

2.11.3

##### Background therapy

2.11.3.1

Standard Western medical treatment will be provided according to the *2024 Chinese Guidelines for the Diagnosis and Treatment of Heart Failure* (28), and a set of principles for medication management and adjustment will be formulated.
(1)Principle of stable baseline medicationBefore randomisation, all subjects are required to undergo a stabilisation period of at least 2–4 weeks on guideline-directed medical therapy (GDMT), and the medication regimen at the end of this stabilisation period is defined as the “baseline treatment regimen”. Criteria for medication stability are: (i) no arbitrary change in drug class; (ii) the dosage of any individual drug should not fluctuate by more than 25% relative to the recent stable regimen.(2)Principles for adjustment of drug class and dosageThroughout the trial, investigators are strongly encouraged to maintain the baseline medication regimen unchanged. If the initiation of any new core heart failure therapy, particularly sodium–glucose co-transporter 2 inhibitors (SGLT2i), angiotensin receptor–neprilysin inhibitors (ARNI), and mineralocorticoid receptor antagonists (MRA), becomes necessary due to newly emerging serious clinical indications, approval must be obtained from the principal investigator (PI) of the participating centre, and the event must be documented as a major protocol deviation, which will be excluded in sensitivity analyses performed in the final statistical analysis. Loop diuretic doses may be adjusted at any time to manage volume status; however, if the diuretic dose increases by >50% from baseline and persists for more than 72 h, this will be classified as a “major medication adjustment”. For medications used to treat comorbidities, the drug class and dosage should remain unchanged in the absence of safety concerns; if adjustment is truly necessary, it should be strictly in accordance with clinical guidelines, and the adjustment should be recorded.(3)Criteria for initiation of rescue therapyTo ensure patient safety while maintaining the integrity of the modified intention-to-treat (mITT) analysis set, rescue therapy should be initiated if any of the following criteria are met: (i) worsening signs or symptoms of heart failure requiring temporary intravenous diuretic use or hospitalisation for heart failure; (ii) an increase in loop diuretic dose of ≥30% from baseline at two consecutive visits, or a single dose up-titration of ≥100%; (iii) sustained weight gain of ≥2 kg within 7 days after increasing the oral diuretic dose; (iiii) symptomatic hypotension (systolic blood pressure <90 mmHg) or a decline in estimated glomerular filtration rate (eGFR) of >30% from baseline, induced by standard pharmacotherapy.(4)Documentation standards for medication adjustmentsAt each study visit (screening, baseline, weeks 4, 8, 12, 18, and 24), all concomitant medications and any adjustments must be recorded completely and in detail in the case report form (CRF). The documentation should include the medication name, dose, frequency, start and end dates of administration, and the reason for the adjustment.(5)Pre-specified subgroup stratification and statistical adjustment strategyRandomisation stratification factor: baseline use of sodium–glucose co-transporter 2 inhibitors (SGLT2i) will be added as a mandatory stratification factor at the randomisation stage (stratified as “used” vs. “not used”). Subgroup analyses: pre-specified subgroup analyses will be performed to examine the treatment effect of the study intervention on peak oxygen consumption (peak VO_2_), according to baseline exposure to SGLT2i and glucagon-like peptide-1 receptor agonists (GLP-1 RAs). Statistical adjustment plan: to control for residual confounding, major medication adjustments and cumulative diuretic exposure (uniformly converted to furosemide equivalent doses) will be included as time-varying covariates in the mixed-effects model for the primary endpoint. In addition, a per-protocol sensitivity analysis will be conducted, excluding subjects with major protocol violations.

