
### Missing data and protocol deviation handling

2.17

For the primary endpoint, the MMRM provides valid estimates under the missing-at-random (MAR) assumption using all available observed data. To test the robustness of the MAR assumption, two sensitivity analyses will be performed: (i) complete-case analysis, restricted to patients who completed the full 24-week follow-up; and (ii) worst-case scenario analysis, in which missing values in the SXYX group are imputed with the minimum observed value and those in the placebo group with the maximum observed value. For secondary endpoints with a missing rate >10%, multiple imputation (MI) using a chained-equation approach will be applied, with the imputation model including all covariates and outcome variables. For patients who meet the mITT criteria (i.e., have received at least one dose of the study drug and have at least one post-baseline CPET assessment), if they experience any of the following events—(i) premature discontinuation of the study drug, (ii) receipt of rescue therapy for worsening heart failure (e.g., intravenous diuretics), (iii) hospitalisation for any reason, (iiii) Medication adjustments due to various reasons, or (iiiii) inability to complete CPET—they will still be retained in the mITT set (in accordance with the intention-to-treat principle), but will be excluded from the per-protocol set for sensitivity analyses. All protocol deviations will be summarised and listed by treatment group, and submitted to the Data Monitoring Committee for review in the final report.

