### Statistical analysis

2.18

Statistical analyses will be performed using SPSS Statistics 32.0 (IBM Corp., Armonk, NY, USA) and R 4.2 (for mixed models). Three analysis populations are defined: (i) the modified intention-to-treat (mITT) set, comprising all randomized patients who received at least one dose of the study drug and had at least one post-baseline primary efficacy assessment—this serves as the primary analysis set; (ii) the per-protocol set (PPS), including patients who completed the 24-week trial without major protocol deviations, used for sensitivity analyses; and (iii) the safety set (SS), including all patients who received at least one dose of the study drug, used for safety analyses. Baseline and descriptive analyses: Baseline demographic and clinical characteristics (including age, sex, BMI, aetiology of heart failure, LVEF, NT-proBNP, SGLT2i use rate, etc.) will be compared between the two groups using independent-samples *t*-tests for continuous variables with normal distribution, Mann–Whitney *U* tests for continuous variables with non-normal distribution, or chi-square tests for categorical variables, in order to describe the balance after randomization. For safety analyses, comparisons of the incidence of adverse events between groups will also be performed using chi-square tests or Fisher's exact test. Primary endpoint analysis: The change in peak VO_2_ from baseline to week 24 is designated as the sole primary efficacy endpoint (week 12 change is reclassified as a key secondary endpoint). The primary analysis will be performed using a mixed-effects model for repeated measures (MMRM) rather than ANCOVA, with fixed effects including treatment group, visit (baseline, week 12, week 24), treatment-by-visit interaction, baseline peak VO_2_, baseline SGLT2 inhibitor use (yes/no), and study center. The MMRM was chosen because it uses all available longitudinal data and accounts for the correlation between repeated measurements within each subject, whereas ANCOVA would be limited to a single post-baseline time point and would not adequately handle the repeated-measure structure. Subject is included as a random effect (random intercept). The treatment effect will be reported as adjusted least-squares mean difference with 95% confidence intervals. Secondary endpoint analysis: Key secondary endpoints (including change in peak VO_2_ at week 12, NT-proBNP, 6-minute walk test, and NYHA functional class) will be analyzed using the same MMRM for continuous variables or logistic regression for categorical variables (with NYHA class dichotomized as improvement ≥1 grade vs. no improvement). To control type I error inflation due to multiplicity, a fixed-sequence testing procedure is prespecified: formal hypothesis testing for these four key secondary endpoints will proceed only if the primary endpoint (week 24 peak VO_2_) is statistically significant (*P* < 0.05), in the following order: ① week 12 peak VO_2_ change → ② NT-proBNP → ③ 6MWT → ④ NYHA class improvement (≥1 grade). All other secondary endpoints (including echocardiographic parameters, TCM syndrome score, individual symptoms/signs, EQ-5D, and coagulation function) are designated as exploratory/supportive endpoints, for which only descriptive statistics and unadjusted *P*-values will be reported; between-group comparisons for these exploratory endpoints will be performed using *t*-tests or Mann–Whitney *U* tests as appropriate, with unadjusted *P*-values provided for descriptive reference only, explicitly labelled as hypothesis-generating and not subject to formal inferential conclusions; hence, no multiplicity adjustment is applied to them. Center heterogeneity: Study center is included as a fixed effect in all MMRM models to account for potential variations in CPET execution, background care, and baseline characteristics across sites, ensuring robustness of the pooled treatment estimate.

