The composition of SXYX follows a rigorous principle of herb compatibility. The sovereign herbs, raw *Hedysarum Multijugum Maxim*, *Codonopsis Radix*, and *Cimicifugae Rhizoma*, supplement Qi and elevate sunken Qi, and carry the effects of the formula upward. The minister herbs, *Radix Paeoniae Rubra*, *Curcumae Rhizoma*, *Trichosanthes Kirilowii Maxim*, *Allium Azureum Ledeb*, *Arum Ternatum Thunb*, and *Radix Bupleuri*, activate blood circulation and resolve stasis, as well as eliminate phlegm and remove turbidity. The assistant herbs, *Cinnamomi Ramulus* and *Lepidii Semen Descurainiae Semen*, unblock Yang, transform Qi, and promote diuresis; *Anemarrhenae Rhizoma* clears heat and nourishes Yin, counterbalancing the warm-dry nature of the Qi-supplementing herbs. The messenger herb, *licorice*, harmonizes the actions of the various ingredients and protects the middle burner (spleen and stomach). The overall effect of the formula is to supplement Qi and activate blood circulation, making it particularly suitable for treating HFpEF with the syndrome of Qi deficiency and blood stasis. HFpEF is secondary to comorbidity-driven systemic inflammation, progressive fibrosis, and myocardial cell injury (31). Preclinical evidence has suggested that flavonoids derived from *Astragalus membranaceus* inhibit Th1 and Th17 cell differentiation and increase regulatory T cell (Treg) levels, thereby reducing inflammatory damage (34). It has also been shown in animal studies that astragaloside IV and *Astragalus* polysaccharide (APS) regulate the aberrant activation of the TGF-β1/Smads pathway, downregulate p38 MAPK and NF-κB/p65 phosphorylation levels, and inhibit myocardial fibrosis (35). Additionally, studies based on isolated compounds have indicated that total paeony glycoside (TPG) inhibits the activation of the NLRP3 inflammasome and alleviates the inflammatory response (36). Similarly, experimental evidence suggests that the β-sitosterol component of Gualou Xiebai Banxia Decoction reduces the levels of IL-1β, IL-6, and TNF-α in endothelial cells, thereby inhibiting inflammatory responses, cardiomyocyte apoptosis, and myocardial fibrosis (37, 38). Preclinical data have also demonstrated that cinnamaldehyde exerts anti-inflammatory effects by modulating multiple signaling pathways, including TLR4, TRAF6, NF-κB, JAK/STAT, and Nrf2, through the regulation of inflammatory cytokines such as TNF-α, IL-1β, and IFN-γ (39). Furthermore, findings from rodent models suggest that the aqueous extract of *Lepidii Semen Descurainiae Semen* (Tinglizi) activates the PI3K/Akt/mTOR signaling pathway, inhibits apoptosis, and ameliorates ventricular remodeling in rats with heart failure (40). Finally, one preclinical study has shown that Shengxian Yixin Granule inhibits myocardial fibrosis, delays ventricular remodeling, and improves cardiac function in rats with myocardial infarction via the PI3K/AKT signaling pathway (41). Taken together, it may be hypothesized that SXYX could exert its therapeutic effects on HFpEF through multiple pathways, including the inhibition of inflammatory responses, myocardial fibrosis, and apoptosis. However, it is important to note that the above mechanistic evidence is primarily derived from individual herbs, isolated compounds, or animal models; these findings should be interpreted as providing biological plausibility rather than proof of the mechanism of action of the complete SXYX formula in patients with HFpEF. Confirmation of these mechanistic hypotheses in the current human trial is warranted.

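### The primary model is specified inconsistently, and the version with post-randomisation medication covariates can bias the treatment effect if SXYX changes medication use

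*Protocol article*

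**What the plan says.** Section 2.11.3.1, item (5), gives a statistical adjustment plan. Its purpose is "to control for residual confounding, major medication adjustments and cumulative diuretic exposure (uniformly converted to furosemide equivalent doses"), and these variables "will be included as time-varying covariates in the mixed-effects model for the primary endpoint". A per-protocol sensitivity analysis is announced separately afterwards, so the covariates belong to the primary model.

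Item (2) of the same section shows what drives them. "Loop diuretic doses may be adjusted at any time to manage volume status", and "if the diuretic dose increases by >50% from baseline and persists for more than 72 h, this will be classified as a" major medication adjustment. Both variables are therefore recorded during treatment.

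Section 2.18 specifies the primary MMRM with treatment group, "visit (baseline, week 12, week 24), treatment-by-visit interaction, baseline peak VO_2_, baseline SGLT2 inhibitor use (yes/no), and study center", plus a random intercept for subject. Neither medication covariate is named.

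Section 2.17 covers mITT patients who stop study drug, receive rescue therapy, are hospitalised or have their medication changed: "they will still be retained in the mITT set (in accordance with the intention-to-treat principle").

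**The concern.** There are two problems.

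**Specification.** The article describes one primary model in two places with different covariates. An analyst following Section 2.18 and one following Section 2.11.3.1 could fit different models. The choice also reaches beyond the primary endpoint: Section 2.18 uses the same MMRM for the continuous key secondary endpoints and opens the fixed testing sequence only if the primary result has P < 0.05.

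**Choice of covariates.** Diuretic dose follows volume status. The Discussion says that two assistant herbs in the formula "unblock Yang, transform Qi, and promote diuresis", so an effect of SXYX on diuretic need is plausible on the protocol's own account. A covariate that treatment can change may act as a mediator, and adjusting for it then takes out part of the effect. It may also share an unmeasured cause with peak VO2, such as worsening heart failure, and adjusting for it then induces an association between arm and that cause. In either case the coefficient no longer estimates the effect regardless of medication changes, which is the estimand that Section 2.17 implies. No other estimand is stated for it.

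**Working it through.** **1. Reproduce the plan's figure (Section 2.2).** Inputs: δ = 2.7; SDs 4.8 and 4.2; z-values 1.96 and 1.282.

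- σ² = (4.8² + 4.2²)/2 = 20.34, so σ = 4.51.
- n = 2 × (1.96 + 1.282)² × 20.34 / 2.7² = 58.65, rounded up to 59 per group.
- 59/(1 − 0.20) = 73.75, rounded up to 74 per group, 148 in total.
- SE of the difference at 59 per group = 4.51 × √(2/59) = 0.830. Power = Φ(2.7/0.830 − 1.96) = 90.2%.

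The stated sample size reproduces.

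**2. Mediated share.** Suppose a share s of the 2.7 passes through the covariates and adjustment removes all of it. The coefficient is 2.7 × (1 − s), and power is Φ(coefficient/0.830 − 1.96). The values of s are assumptions; the document gives none.

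| s (assumed) | Coefficient | Power at 59 per group |
|---|---|---|
| 0 | 2.70 | 90% |
| 10% | 2.43 | 83% |
| 20% | 2.16 | 74% |
| 30% | 1.89 | 62% |

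**3. Simulation with a shared cause.** This was a linear model at a single time point with 1,000,000 patients per scenario. All inputs other than σ and δ are assumed. Latent worsening (SD 1) lowers peak VO2 by b = 1, 2 or 3 mL/kg/min per SD. It also drives both an escalation indicator (about 21% of placebo patients) and a diuretic dose. SXYX lowers worsening by a SDs, and the true total effect is fixed at 2.7. The model adjusts for both covariates.

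| a (assumed) | Adjusted coefficient, b = 1 / 2 / 3 | Power at 59 per group |
|---|---|---|
| 0 | 2.69 / 2.69 / 2.70 | 90% |
| 0.3 | 2.55 / 2.38 / 2.21 | 87% / 82% / 76% |
| 0.6 | 2.40 / 2.12 / 1.83 | 82% / 73% / 60% |

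**4. Zero effect on peak VO2.** Here SXYX lowers only the prescribing of diuretics, by k on the same scale.

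- k = 0: the adjusted coefficient is within 0.03 of zero and type I error is 5%.
- k = 0.3: −0.14, −0.32 and −0.48 for b = 1, 2 and 3; approximate two-sided type I error 5%, 7% and 9%.
- k = 0.6: −0.28, −0.59 and −0.87; approximate type I error 6%, 11% and 18%.

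The power and type I error figures hold the SE at 0.830. They ignore any change in precision from the adjustment and do not reproduce the repeated-measures structure of the MMRM.

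**The case against.** **The list in Section 2.18 may be open.** It is introduced as including the named effects, so Section 2.11.3.1 could be read as adding to it. A reader might infer a flat contradiction, and the wording does not quite support that. But the open reading does not rescue the plan: the post-randomisation adjustment then simply applies.

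**Bias is conditional.** A reader might infer that the adjustment always removes effect, or biases the estimate even when SXYX does nothing. It does not. With no effect on medication use the covariates are balanced in expectation, and the rows with a = 0 and k = 0 show no bias. The zero-effect case in step 4 still assumes that SXYX changes prescribing.

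**Section 2.17 concerns set membership.** A reader might infer that the adjustment undoes the intention-to-treat set. A covariate removes nobody from the mITT set. The tension is only about what the coefficient estimates.

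**Randomisation does not settle everything.** The mITT set requires a post-baseline primary efficacy assessment and 20% dropout is expected, so the analysed groups are not exactly the randomised ones. That is true, but adjusting for variables that treatment may itself change does not repair it.

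**The size is easily overstated.** If the covariate is a noisy proxy for congestion with assumed within-arm correlation r of 0.3–0.6, adjustment removes r², or 9–36%, of the part of the effect that runs through congestion. Applied to all of 2.7 this gives 0.24–0.97. But the Discussion hypothesises that SXYX acts through inflammation, fibrosis and apoptosis, and credits diuresis only to assistant herbs. If half the effect ran through congestion, the range would be 0.12–0.49.

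**Conclusion.** The point holds in a conditional form. The primary model is inconsistently specified between Sections 2.11.3.1 and 2.18; this rests on the text alone. The Section 2.11.3.1 version can bias the total effect if SXYX alters medication or diuretic use, which is plausible from the protocol's rationale but not established.

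The size cannot be derived from the document. Under the assumed 10–30% mediated share, the loss is 0.27–0.81 mL/kg/min of 2.7, and power drops to 83–62%. Every scenario lets SXYX lower worsening or diuretic use or leave it unchanged, and the bias is then nil or against SXYX. The harm shown is lost power or a spurious unfavourable result. A reader might infer a risk of a false efficacy claim, but these scenarios do not show one; the opposite case, in which SXYX raises medication use, was not examined.

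The matter still needs settling before unblinding, because it defines the sole primary analysis and the gate to the key secondary tests.

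**What to change.** Delete the time-varying covariates from the primary model in Section 2.11.3.1, item (5), so that the only covariates are the baseline ones of Section 2.18: peak VO2, SGLT2 inhibitor use and centre. Report major medication adjustments and furosemide-equivalent dose by arm. If the effect without background-drug change is of interest, present it as a supplementary analysis with a stated hypothetical estimand and a method suited to post-randomisation variables. Setting values after the change to missing and imputing them is one option among several.

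The cost is a small amendment to a protocol that already has ethics approval and registration. The sample size stays at 59 per group before dropout and 148 in total.

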
##### SXYX group

2.11.3.2

On the basis of background therapy, patients will additionally receive SXYX Granule, taken with warm water after a 0.5-hour interval following Western medications. The dosage is one bag per dose, three times daily (morning, midday, and evening). The treatment duration is 24 weeks.

##### Placebo group

2.11.3.3

On the basis of background therapy, patients will additionally receive a placebo matching SXYX Granule. The administration method and treatment duration are the same as those in the SXYX group.

### Investigational drug management

2.12

The study team will initially distribute the investigational drug to each center according to its expected enrollment schedule and record the distribution. Subsequent shipments will be dynamically adjusted based on actual enrollment progress, and an inventory alert threshold will be set (e.g., when the stock falls below a 2-week supply) to prevent drug shortages. In this double-blind trial, the site drug administrator at each study center will be responsible for drug dispensing and patient instruction on proper use. The drug packaging and labeling comply with blinding and randomization requirements, and measures will be taken to ensure the drug does not deteriorate during storage and transportation. After the trial is completed, the site drug administrator will collect and count the remaining drug and return it to the study team.

Medication adherence will be calculated as (actual dose taken ÷ expected dose) × 100%. Adherence between 80% and 120% is considered good. The actual dose taken is calculated as: dispensed amount − returned amount − lost amount. For patients with poor adherence, the reasons should be identified and documented.

